**Methods/design:**

The RESPECT study is a nationwide population-based prospective, controlled, mixed-methods intervention study looking at children aged 6-18 years newly diagnosed with cancer in eastern Denmark (n = 120) and a matched control group in western Denmark (n = 120). RESPECT includes Danish-speaking children diagnosed with cancer and treated at pediatric oncology units in Denmark. Primary endpoints are the level of educational achievement one year after the cessation of first-line cancer therapy, and the value of VO_2max_ one year after the cessation of first-line cancer therapy. Secondary endpoints are quality of life measured by validated questionnaires and interviews, and physical performance. RESPECT includes a multimodal intervention program, including ambassador-facilitated educational, physical, and social interventions. The educational intervention includes an educational program aimed at the child with cancer, the child’s schoolteachers and classmates, and the child’s parents. Children with cancer will each have two ambassadors assigned from their class. The ambassadors visit the child with cancer at the hospital at alternating 2-week intervals and participate in the intervention program. The physical and social intervention examines the effect of early, structured, individualized, and continuous physical activity from diagnosis throughout the treatment period. The patients are tested at diagnosis, at 3 and 6 months after diagnosis, and one year after the cessation of treatment. The study is powered to quantify the impact of the combined educational, physical, and social intervention programs.

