### Participants

Children aged 6-18 years diagnosed with cancer and treated with chemotherapy/irradiation, or diagnosed with Langerhans cell histiocytosis (LCH) or myelodysplastic syndrome (MDS) and treated with chemotherapy, at any pediatric oncology unit in Denmark are eligible for the study. All participants are enrolled at school at the time of diagnosis and are able to communicate in Danish. Children with mental disability (e.g. Down syndrome), severe co-morbidity, or terminal illness at the time of diagnosis are excluded. Patients diagnosed in the period 2013-2015 at the Copenhagen University Hospital Rigshospitalet (n = 120), are assigned to the intervention group.

Four control groups are identified: 1) children with cancer diagnosed at Odense University Hospital, Aarhus University Hospital, and Aalborg University Hospital in the period 2013-2015 (n = 120). Secondary control groups are 2) the sibling closest in age (regardless of gender) to the child with cancer, and 3) the child’s classmates. In addition, we include 4) a historical nationwide control group of children with cancer treated from February to December 2012 (n = 113 families).

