### Statistical considerations I

We expect all children aged 6-18 years diagnosed with cancer in Denmark during 2013-2015 will be included in the study. The primary endpoint for school achievement is classified using five ordinal categories: outstanding level of performance, high level of performance, satisfactory level of performance, needs improvement in level of performance, and unsatisfactory level of performance, with the frequency distribution of these five categories being 10%, 20%, 40%, 20%, and 10%, respectively (Figure 1). A change from one category to another is considered a significant change in the child’s school achievement (e.g. high level of performance to satisfactory level of performance). This endpoint will be analyzed using an ordinal regression model (details are given in Additional file 1) [53,54]. The primary endpoint of VO_2max_ in the intervention and control groups is determined by comparing the scores at diagnosis to the scores at one year after the cessation of treatment. This is done using an independent samples t-test. Additional analyses using the four study time points (diagnosis, 3 months after diagnosis, 6 months after diagnosis, and one year after cessation of treatment) will also be performed. Means and 95% confidence limits for the intervention and control groups will be computed at each time point using linear mixed models and the trajectories will be analyzed. A similar method will be used for the secondary endpoints but using only three time points for the questionnaire data. Linear mixed models will be used for each subscale of the PedsQL Core, the SDQ, the RCADS, Resilience, and the LDQ, and for the Andersen test, the timed Up-and-Go test, and the hand strength measurement. For the count data (the sit-to-stand test and the flamingo balance test), Poisson regression models with random effects will be used. Because the study is not randomized all comparisons of the two groups will be controlled for diagnosis. If any other variables are found to be unevenly distributed across the two groups additional analyses controlling for the effects of these variables will also be considered.

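### In a non-randomised comparison, covariates other than diagnosis are adjusted for only if found unbalanced, and only in optional extra analyses; the set should be fixed in advance

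*Protocol article*

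**What the plan says.** The Participants section forms both groups by hospital and calendar period. For the intervention: "Patients diagnosed in the period 2013-2015 at the Copenhagen University Hospital Rigshospitalet (n = 120), are assigned to the intervention group". For the primary controls: "children with cancer diagnosed at Odense University Hospital, Aarhus University Hospital, and Aalborg University Hospital in the period 2013-2015 (n = 120"). No matching variable is named. Statistical considerations I adds: "We expect all children aged 6-18 years diagnosed with cancer in Denmark during 2013-2015 will be included in the study". The Abstract nevertheless describes "a matched control group in western Denmark (n = 120").

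On adjustment, Statistical considerations I makes one firm commitment: "Because the study is not randomized all comparisons of the two groups will be controlled for diagnosis". For other variables the rule begins "If any other variables are found to be unevenly distributed across the two groups additional analyses controlling for the effects of these variables" and ends by saying that analyses "controlling for the effects of these variables will also be considered". It names no candidate variable and no criterion for uneven distribution.

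The same section tests the primary VO2max endpoint, the change from diagnosis to one year after treatment ends, with an independent samples t-test. Linear mixed models over four time points are additional. School achievement is analysed by ordinal regression, with details in Additional file 1, which is not shown.

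**The concern.** The article does not leave the adjustment set to a later document. It states a rule, and the rule has three weaknesses.

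- **The trigger looks at the wrong quantity.** Confounding bias is roughly the group difference in a covariate multiplied by that covariate's effect on the outcome. A modest imbalance in a strong predictor can bias more than a large imbalance in a weak one, yet only the latter is sure to attract attention.
- **The choice is made after the data are seen.** With no variable list and no criterion, several adjusted and unadjusted results could each be defended afterwards.
- **Nothing follows for certain when imbalance is found.** The adjusted analysis is additional and optional, so the primary result stays as it was.

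At stake is whether a difference between eastern and western Denmark can be read as an effect of the programme. The word matched adds to this in a small way, because it suggests a comparability that the described design does not create.

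**Working it through.** **1. The text, side by side.** All comparisons are to be controlled for diagnosis, but the primary VO2max test is a two-sample t-test, which has no place for diagnosis or any other covariate. The two statements stand in the same section and cannot both be carried out as written. Likewise, the Abstract says matched, while the Methods define controls by hospital and period and expect every eligible child to be included, which leaves no room for individual matching.

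**2. The plan's own figure.** Inputs from Statistical considerations II: 120 per group, SD of change 5.3, significance level 0.025, target 10% of 24.3 = 2.43 ml/min/kg.
- SE of the difference = 5.3 × √(2/120) = 0.684.
- Two-sided critical value at 0.025 = 2.241.
- Power = Φ(2.43/0.684 − 2.241) = Φ(1.310) = 0.905.

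The stated 0.90 is reproduced, so the point does not rest on a wrong sample size. The one-sided version gives 0.944, so the two-sided reading is the one that fits.

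**3. Would an imbalance check notice a modest gap?** Assumption: ages spread evenly over the whole years 6 to 18.
- SD of age = √((13² − 1)/12) = 3.74 years.
- SE of the difference in mean age = 3.74 × √(2/120) = 0.483.
- An underlying half-year gap is 0.5/0.483 = 1.04 SE. A 5% test would flag it with probability Φ(1.04 − 1.96) + Φ(−1.04 − 1.96) ≈ 0.18.

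The same holds for a binary factor with prevalence near 50%. With 120 per group, a 5% test detects a 10-point difference 34% of the time.

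**4. What the missed gap does to the primary test.** Further assumption: VO2max change varies by 0.5 to 1.0 ml/min/kg per year of age. With bias b = gap × slope, the error rate is Φ(−2.241 + b/0.684) + Φ(−2.241 − b/0.684).

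| Age gap | Slope | Bias b | Share of 2.43 | Error rate |
|---|---|---|---|---|
| 0.5 year | 0.5 | 0.25 | 10% | 0.030 + 0.005 = 0.035 |
| 0.5 year | 1.0 | 0.50 | 21% | 0.065 + 0.001 = 0.067 |

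The upper slope is a strong assumption. It implies that age explains (1.0 × 3.74/5.3)² = 0.50 of the variance of the change score, against 0.12 for the lower slope.

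**The case against.** Several limits are fair, and they rule out stronger readings.

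- **That the primary comparisons have no protection.** A reader might infer this, but the text does not support it. Control for diagnosis is promised for all comparisons, and the VO2max change score already subtracts a difference in baseline level, though not regression to the mean or an effect of age or sex on the change itself.
- **That school achievement is analysed without its baseline.** This cannot be concluded. The ordinal model is set out in Additional file 1 and a figure, neither of which is shown, and its covariates may already include the rating at diagnosis. For that endpoint the point rests only on the general rule.
- **That the error rate could reach about 22%.** A 1-year gap with the steepest slope gives b = 1.0 and an error rate of 0.218. But a 1-year gap is 2.1 SE, which a 5% check would more likely than not flag (Φ(2.07 − 1.96) ≈ 0.54), and no age gap or slope is documented. It should not be used as the size of the problem.
- **That an imbalance check means a significance test.** The article names no test. A rule based on standardised differences could flag half a year (0.5/3.74 = 0.13 SD). This stands, but it shows how much depends on a criterion that the rule does not state.
- **That the baseline value belongs in every model.** It does not. The mixed models use diagnosis as a response time point.
- **That matched misleads about the analysis.** The word occurs in the Abstract, while the Methods define the groups plainly and the statistics section says that the study is not randomised. It is a wording fault.

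The documents also do not name age or sex as prognostic. They are a reviewer's choice, reasonable for an age range of 6 to 18.

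**Conclusion.** The point holds for the rule as written. Beyond diagnosis, adjustment is triggered by observed imbalance, confined to additional analyses, and optional even then. The conflict between the promise to control for diagnosis and the t-test for VO2max follows from the text alone, as does the lack of any described matching.

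The size is illustrative. A half-year regional age gap gives a bias of 0.25 to 0.5 ml/min/kg, or 10% to 21% of the target difference, and an error rate of about 3.5% to 6.7% against 2.5%. This depends on the assumed age distribution, gap and slope. The sponsor should change the rule, but the case for doing so rests on its form and not on these figures.

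**What to change.** - Delete the imbalance trigger. Pre-specify one adjustment set (diagnosis group, age and sex) for the primary and secondary between-group models, whatever imbalance is observed.
- Replace the t-test for the primary VO2max comparison with a regression carrying that set, either of the change score or of the one-year value with baseline VO2max as a covariate. Choose one in advance, because in a non-randomised comparison the two can answer different questions. The change score stays closest to the sample size calculation.
- In the mixed models, keep the value at diagnosis as a response time point and do not also enter it as a covariate.
- For school achievement, include the rating at diagnosis if it is collected and Additional file 1 does not already include it.
- In the Abstract, delete matched or describe an unmatched concurrent regional control group.

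The cost is analysis wording, a few degrees of freedom, and a change of the primary VO2max test to a regression. The article already records demographics by questionnaire and tests VO2max at diagnosis. It does not say clearly that a school rating is collected at diagnosis, so that item needs checking.

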**Figure 1 F1:**
[figure not shown]
The structure of the ordinal regression model.

### Statistical considerations II and sample size calculations

This study has two primary endpoints therefore the type I error is set at 0.025 in the sample size calculations. For the primary endpoint in the educational intervention the ordinal regression model with a power of 0.90 outlined in Additional file 1 will to be able to detect a shift in the ordinal rating of approximately ½ a point, yielding a marginal frequency distribution for the five categories of 6%, 13%, 32%, 25%, 24%. Details are provided in Additional file 1.

The primary endpoint of the physical and social activity study is based on the power calculation derived from a pilot study [25] that found a baseline VO_2max_ of 24.3 ml/min/kg (SD 5.9) among children with acute lymphoblastic leukemia. If 120 children with cancer are included in both the intervention and control group, if the standard deviation of the change scores is 5.3 in both groups, and we use a significance level of 0.025, we will have a power of 0.90 to detect a 10% increase in the intervention group one year after cessation of treatment.

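### The equal 0.025 split across two primary endpoints has no step-down; Holm would keep family-wise error at 0.05 and gain power on each endpoint and on both

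*Protocol article*

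**What the plan says.** Under Statistical considerations II and sample size calculations, the protocol article gives both the split and its reason: there are two primary endpoints, "therefore the type I error is set at 0.025 in the sample size calculations". The VO2max power statement repeats the level: "we use a significance level of 0.025, we will have a power of 0.90 to detect a 10% increase in the intervention group". The education endpoint is also given a power of 0.90, through an ordinal model whose details are in Additional file 1, which is not shown.

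Statistical considerations I names the two primary analyses: an ordinal regression for school achievement and an independent samples t-test for VO2max. It gives no rule for using the result of one primary test when judging the other. Neither section says whether 0.025 is one-sided or two-sided.

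**The concern.** The article chose an equal Bonferroni split and sized the study on it. Used as a fixed threshold for both final tests, that split is dominated. Holm rejects whenever fixed 0.025 rejects, sometimes rejects more, and keeps the same family-wise error limit.

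The loss falls mainly on showing both effects. That matters here because each endpoint belongs to one arm of a combined programme, and the Abstract and Conclusion present the study as powered for the combined educational, physical and social intervention.

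**Working it through.** **Inputs.** From Statistical considerations II: 120 children per group, SD of change 5.3, baseline VO2max 24.3 ml/min/kg, a 10% increase (0.10 × 24.3 = 2.43), level 0.025, and power 0.90 for each endpoint. The correlation between the two test statistics is not given; 0, 0.3 and 0.5 are assumed.

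**1. The plan's own VO2max power.**
- Standard error = 5.3 × √(2/120) = 0.684.
- Standardised effect = 2.43 / 0.684 = 3.551.
- Two-sided 0.025: Φ(3.551 − 2.241) = 0.905 (0.902 with the noncentral t). This reproduces the stated 0.90.
- One-sided 0.025 gives 0.944, which does not fit, so 0.025 is read as two-sided.

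**2. Family-wise error under Holm at overall 0.05.**
- Both nulls true: a false claim needs the smaller p-value to be at or below 0.025. Its probability is at most 0.025 + 0.025 = 0.05.
- One null true: that endpoint can be rejected only if its p-value is at or below 0.05, so the probability is at most 0.05.
- Both bounds hold under any dependence. In simulation, the error with both nulls true was about 0.049 at correlation 0 and 0.046 at correlation 0.5. With one null true it was at most about 0.0475.

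**3. Power by hand, independent endpoints, each with power 0.90 at 0.025.**
- Non-centrality = 2.2414 + 1.2816 = 3.523.
- Power at 0.05 = Φ(3.523 − 1.960) = 0.941, so the chance that p lies between 0.025 and 0.05 is 0.941 − 0.90 = 0.041.
- Holm, each endpoint: 0.90 + 0.041 × 0.90 = 0.937.
- Both under fixed 0.025: 0.90² = 0.81.
- Both under Holm: 0.941² − 0.041² = 0.884.
- At least one, either rule: 1 − 0.10² = 0.99. Holm's first step uses the same 0.025, so it cannot change this figure.

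**4. Effect of correlation.** Simulation of 2 million pairs of normal test statistics, with power at 0.025 of 0.905 for VO2max and 0.90 for education:

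| Assumed correlation | Rule | VO2max | Education | Both | At least one |
|---|---|---|---|---|---|
| 0 | Fixed 0.025 | 0.905 | 0.900 | 0.815 | 0.991 |
| 0 | Holm | 0.940 | 0.937 | 0.887 | 0.991 |
| 0.3 | Fixed 0.025 | 0.905 | 0.900 | 0.826 | 0.979 |
| 0.3 | Holm | 0.937 | 0.934 | 0.891 | 0.979 |
| 0.5 | Fixed 0.025 | 0.905 | 0.900 | 0.836 | 0.969 |
| 0.5 | Holm | 0.934 | 0.931 | 0.897 | 0.969 |

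**5. If the education power is lower.** The stated 0.90 cannot be checked without Additional file 1. As an illustration only, a simulated unadjusted Wilcoxon comparison of the two printed distributions, 120 per group, has power 0.846 at 0.025 and 0.903 at 0.05. With VO2max at 0.905 and 0.944 and independence, power for both goes from 0.905 × 0.846 = 0.77 to 0.944 × 0.903 − 0.039 × 0.057 = 0.85. The gain does not depend on the 0.90 being exact.

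**The case against.** The strongest reply is that Bonferroni is valid, the study was sized to have 0.90 power per endpoint under it, and leaving out a refinement is not an error. That stands, and it sets the weight of the point: the plan as stated controls the error, and Holm is an optional gain. An analysis plan that is not shown may also already contain a step-down. Still, the article chose the split and gave its reason, so it is fair to say that a uniformly better version of the same choice is available.

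The gain is also modest: 3 to 4 percentage points per endpoint, 6 to 7 for both, none for at least one. The larger gain for both assumes independence, although the same children provide both endpoints; at correlation 0.5 it is about 6 points. Holm also helps one endpoint only when the other is significant at 0.025.

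A reader might infer something stronger: that 0.025 applies to the sizing alone, that the final tests will run at 0.05, and that the planned 95% limits confirm this, giving a family-wise error of 1 − 0.95² = 0.0975. The documents do not support this. The sentence "Means and 95% confidence limits for the intervention and control groups will be computed at each time point" concerns each group's mean in mixed models that are introduced as additional analyses. It does not give limits for a primary between-group contrast, and it does not conflict with a 0.025 test. Nothing in the article says that either primary endpoint will be tested at 0.05, and power computed at 0.025 most naturally describes a test at 0.025. Holm is therefore not needed to secure error control.

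**Conclusion.** The point holds as a low-cost improvement. Fixed 0.025 for both primary endpoints keeps family-wise error at or below 0.05, and so does Holm, under any dependence. With the stated design power, Holm raises each endpoint from about 0.90 to about 0.94 (0.93 at correlation 0.5). Power for both rises from about 0.81 to 0.88 under independence, or from about 0.84 to 0.90 at correlation 0.5.

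These figures assume that 0.025 is two-sided, that the test statistics are approximately normal, that the education endpoint's power is as stated, and that the correlation lies in the assumed range. Holm deals with multiplicity only; it does nothing about confounding in this non-randomised comparison.

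**What to change.** Add to Statistical considerations I that the two primary endpoints are tested by Holm at an overall two-sided 0.05: the smaller p-value against 0.025 and, if that is significant, the other against 0.05. Leave the 0.025 sizing in Statistical considerations II as it is.

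Holm has no simple matching simultaneous intervals. If 97.5% intervals are reported for the two primary contrasts, say that they are Bonferroni intervals. A second endpoint with p = 0.04, for example, would be significant under Holm while its 97.5% interval still included no effect. The 95% limits for the group trajectories need no change.

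The cost is a sentence or two of text and this caveat on intervals. No extra patients or data are needed, and the family-wise error limit is unchanged.

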### Ethical approval

Information on the subjects is protected according to the Processing of Personal Data and Health Act. The Danish Data Protection Agency (file. 2007-58-0015/nr.30-0734) and the Regional Ethics Committee for the Capital Region (file. H 3-2012-105) approved the project, and the project complies with the Helsinki II declaration. In addition, the study is registered at Clinical Trials.gov (file. NCT01772849 and NCT01772862). Following oral and written information, parental, guardian and child’s (children above 15 year) written informed consent was obtained.

## Discussion

RESPECT is based on experience from an unpublished feasibility period, a theoretical framework, and earlier intervention studies of children with cancer, but reliable evidence on rehabilitation in children with cancer is lacking. RESPECT is the first nationwide study with sufficient power to reliably test the impact of a combined multimodal intervention program during treatment. The strength of this study is the combination of educational, psychosocial, and physical components, and the study has a more interactionistic and comprehensive perspective on rehabilitation than most of the previous studies.

Although a randomized trial would be optimal from a scientific point of view, it is unrealistic because the psychological, social, and ethical aspects mean only some of the children at the same unit will have ambassadors.

Another methodological consideration is the intervention starting at diagnosis. Starting an intervention study during the course of very toxic and intensive treatment causes logistical challenges related to the disease and the side effects of the treatment. At the time of diagnosis, families are very vulnerable and stressed, and there is a potential risk of declining participation. However, the feasibility period suggested a participation rate above 90%. Furthermore, the focus on rehabilitation may ameliorate the psychosocial burden on the child. The inclusion of two ambassadors from the child’s school class is unique in childhood cancer rehabilitation, but also carries potential ethical concerns related to the emotional stress and school performance of the ambassadors. The feasibility period indicated that we will be able to allocate two suitable ambassadors to more than 95% of patients, and that they will be able to cope with the challenges linked to their participation. To supervise this group we have an ambassador counsel chaired by a senior child psychologist, who is not involved in the daily operation of the project. Furthermore, an ambassador manual describes the selection procedures, safety measures, and intervention possibilities, to optimize identification and psychosocial monitoring. Before being accepted as an ambassador, and after every visit to the hospital, the ambassadors are screened and have clear follow-up plans arranged. Any adverse events and complications are continuously monitored and recorded.

Although physical exercise may cause sore muscles and stress injuries, there are no reports on such injuries in the existing literature on physical training of children with cancer. Another consideration is the level of intensity to which we exercise and test the children with cancer, from diagnosis and during treatment. Studies among children with heart diseases show that exercise training from low to high intensity is feasible and tolerable for seriously ill children [55] and it may have a positive effect on side effects such as fatigue [56]. While the primary endpoint of the physical intervention is not well documented for this study group, it is the gold standard in healthy children and a common outcome measurement in older cancer patients. The physical activity is adjusted to the treatment intensity and duration as well as the general condition of the child with cancer. During the physical intervention we monitor and assess adverse events.

We believe that RESPECT will contribute vital knowledge to the treatment and rehabilitation of children with cancer as well as other children hospitalized with long-term illness.

